
There will be four evaluation time points. The first evaluation time point will be prior to implementation of the MoB in-person intervention, the second will take place immediately after completion of the MoB in-person intervention, and the third and fourth evaluations will be applied at 6 and 12 months, respectively, after completion of the MoB in-person intervention. These time points have been determined according to the systematic review completed in Stage 1 [14].

The control group will be assessed via the same evaluation tools as the intervention group, and at the same time periods. This will test the null hypothesis that patients who solely receive pharmacotherapy demonstrate the same improvement as the intervention group.

The educational meetings will be held at Cyprus University of Technology in a room specially designed for this purpose that is soundproof, without windows, and chairs placed in a circular arrangement to allow for eye contact, along with small tables on either side to keep notes.

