#### Data Analysis

The means (SD) will be calculated for the scale numeric (sum) scores (YMRS, WHOQOL, MHLC, BDKS, DUDIT, DAI-30, AUDIT, relapse frequency/duration) and frequencies will be calculated for categorical variables (gender, age groups, sex, years in illness groups). Parametric tests (analysis of variance, *t* test) will be applied for comparisons between groups. For all statistical tests, *P* values of .05 or lower will be considered statistically significant. Data will be analyzed through the Statistical Package for Social Sciences (SPSS Inc, version 25.00). To test the relationship between two or more variables, logistic and linear regression analyses will be used. The multiple imputation method will be applied to handle missing data.

### Stage 4

Assessment of the applicability of the MoB digital platform will be based on qualitative (users’ feedback) and quantitative (data analysis) testing. The qualitative assessment will be based on the experience of the users with the platform and on the degree to which they were positively affected by its use. Specifically, the focus of the interviews will be on the impact of the platform on their everyday life, as well as on enhancement of ill health self-management skills according to the participants’ responses to the following open-ended questions: (a) “How would you describe your experience with the use of the MoB digital platform?” (b) “What was the impact of use of the MoB digital platform on your life?” and (c) “What was the impact of the MoB digital platform on your ill health self-management skills?” This process will take place via focus groups discussions. Specifically, two focus groups with 8-12 participants each will be recruited including participants who (a) attended the MoB in-person intervention and had used the platform and (b) solely used the MoB digital platform.

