The quantitative testing involves anonymous questionnaires provided to users of the MoB digital platform, who will have to answer predefined questions regarding satisfaction parameters relevant to the platform. The first outcome assessed will be the level of users’ satisfaction with the MoB digital platform, measured by the score on a 3-item Likert scale (low, moderate/accepted, high) self-questionnaire exploring users’ perceptions of overall experience; utility, according to their present medical condition and clinical state; practicality on daily usage; improvement of self-management skills; and technical difficulties experienced [51]. The second outcome is the degree of improvement in users’ knowledge as measured by the score on the BDKS [50].

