#### MoB Digital Platform

The interactive part of the platform is under development, while the informative part is live [52] and accessible to the participants in the current study, as well as to any interested person (eg, family members of people with BP) or caregivers providing updated information related to BD (platform users). The platform is in the form of a dynamic website with user-generated content as well as static information, following a responsive design (ie, accessible with all types of devices). The informative part, so far, includes the following functionalities: self-management action plan, homework exercises, self-assessment tools, and scientific articles relevant to BD. Entry into the platform functionalities (scientific articles excluded) is password-protected.

Users can register in the platform by filling in their personal profile and can log out/log in and revisit at their convenience. Regarding self-management functionalities, the platform will contain subject units where personal relapse symptoms may be registered, a life events table, personal risk factors for relapse, and a weekly program of activities. Input of relevant information will be provided through open-ended questions and checklists. Participants of the MoB in-person intervention who visit the platform will find that these subject units (chapters) are topics on which they will be educated on. Additional features will be incorporated according to development of Stage 1 (eg, new training needs as described by participants in the focus groups).

Another subject unit will be the personal therapy file, where users will have the chance to keep tabulated notes related to their therapy, including information about the dose and type of medication treatment, as well as pending medical tests (eg, blood tests) and other relevant information. The therapeutic team of the user will have the ability to access the information by registering in the platform under approval of the user with the aim to support continuity and share information.

### Stage 3

The recruitment of the participants of the intervention group (40 patients) and the control group (40 patients) began during the first semester of 2021.

### Stage 4

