User behavior data have been analyzed through Google Analytics by tracking the platform for approximately 1.5 years (January 2019 to October 2020). Specifically, we have recorded that 2180 users have visited the platform with an average session duration of almost 2 minutes. The bounce rate of these visits is 68%, which calls for improvement. The returning visitor rate is approximately 10%, and 70% of the visitors are accessing the platform via mobile and tablet devices.

The website has a total of 7100 page views. Each user has an average of 2.6 pages per visit. In terms of search appearance, it seems that 72% of the traffic is derived from organic searches, which means that search engine optimization fundamentals have been applied to the highest level. Usability testing is being performed to ensure that the website is improving the lives of the users.

The full development and release of the interactive part of the digital platform is expected to be finalized by the second semester of 2022, at which time the assessment of the applicability of the platform will take place.

The timeline of the proposed study is presented in Figure 1.

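### Stage 4 names improvement in BDKS knowledge as an outcome but collects it by anonymous questionnaire with no stated baseline, so a difference in mean score could reflect who responds rather than learning

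*Protocol article*

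**What the plan says.** Methods, Stage 4 opens with the purpose: "Assessment of the applicability of the MoB digital platform will be based on qualitative (users’ feedback) and quantitative (data analysis) testing". The quantitative part is then fixed: "The quantitative testing involves anonymous questionnaires provided to users of the MoB digital platform". Two outcomes follow. The first is satisfaction with the platform. On the second the text says: "The second outcome is the degree of improvement in users’ knowledge as measured by the score on the BDKS".

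Other sections bear on whether these scores could be linked:

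- **Time points.** Effectiveness Evaluation (Stage 3) sets four assessments around the in-person sessions: "The first evaluation time point will be prior to implementation of the MoB in-person intervention". None is given for platform users in Stage 4.
- **Codes.** Data Management gives each participant a unique code built from the assigned group and a sequence number. This covers people assigned to the two Stage 3 groups.
- **Pseudonyms.** Ethics and Data Management says that pseudonyms will be used for study participation.
- **Who the users are.** Results, MoB Digital Platform says the informative part is "accessible to the participants in the current study, as well as to any interested person".
- **Accounts.** The same section says: "Users can register in the platform by filling in their personal profile". The Stage 4 questionnaires are not said to be tied to these accounts.

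**The concern.** Improvement is a difference between two scores, and to be read as learning the two scores should come from the same person. Methods, Stage 4 fixes an anonymous data source and a change outcome, and the two do not fit. If BDKS is given once, no improvement can be measured. If it is given at two times without a link, the only available contrast is the mean of those who answered later against the mean of those who answered first. Users who are better informed or more motivated may be more likely to answer again, and that alone would raise the later mean.

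At stake is any statement that the platform improves knowledge among its users. A later analysis plan cannot repair this, because a link that was not collected cannot be recovered.

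**Working it through.** **1. Is there a figure to reproduce?** No. The article states no sample size, effect size or test for the Stage 4 BDKS outcome. The group comparisons under Data Analysis belong to Stage 3.

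**2. Does any section supply a link or a baseline for Stage 4 users?**

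- The four time points are defined by the in-person sessions, which a platform-only user from the public does not attend.
- The group-and-number codes exist only for people assigned to a Stage 3 group.
- Pseudonyms are promised for study participation, but Methods, Stage 4 does not apply them to these questionnaires, and platform users need not be enrolled.
- Accounts exist, but tying answers to an identifiable account would conflict with calling the questionnaires anonymous.

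So, on the natural reading, there is neither a link nor a stated baseline.

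**3. How large could the artefact be?** The documents do not give the inputs, so this is an illustration on assumptions.

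- Let X be the standardised BDKS score at first use, with mean 0 and SD 1, and let nobody's score change.
- Let the chance of giving a later score be P(x) = 1 / (1 + exp(−(a + b·x))), with b = ln(OR). OR is the odds ratio for giving a later score per SD of BDKS.
- Choose a so that the average of P equals the later-response proportion p.
- The apparent rise in the unlinked mean is E[X·P(X)] / p, found by numerical integration.

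| Later-response proportion p (assumed) | OR 1.0 | OR 1.25 | OR 1.5 | OR 2.0 |
|---|---|---|---|---|
| 10% | 0 | 0.20 SD | 0.36 SD | 0.60 SD |
| 30% | 0 | 0.16 SD | 0.28 SD | 0.44 SD |
| 50% | 0 | 0.11 SD | 0.20 SD | 0.31 SD |

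All of these rises occur with zero learning. Unlinked data cannot show which column applies.

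**4. What does linkage change?** Among people with both scores, the mean of (later − first) is 0 in every cell, because each person is compared with themselves. The shift caused by who answers again drops out. Linkage also allows the first scores of people with and without a later score to be compared, which shows how selective the follow-up was.

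**The case against.** Several points on the other side have force.

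- **Anonymity may not cover the BDKS.** The sentence on anonymous questionnaires explicitly mentions only satisfaction questions. A separate, identified BDKS is not strictly excluded. But the BDKS is listed as the second outcome of the same quantitative testing, so the natural reading covers it.
- **The article may use anonymity loosely.** It promises pseudonyms for study participation, and in Stage 1 it speaks of preserving the anonymity of people whom the researchers meet two or three times. Anonymous could therefore mean not publicly identifiable. This stands as a possibility and is a reason to clarify, but Stage 4 does not say so.
- **Two administrations are inferred.** The article does not describe a before-and-after BDKS in Stage 4. That design follows only from the word improvement. With a single administration the outcome would be less well defined still.
- **Linked data on platform-only patients already exist in the plan.** The Stage 3 control group has the platform alone, has coded records and completes the BDKS at all four time points. This stands and is used in the fix. Stage 4 does not say it draws on those data.

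Two stronger readings are tempting, and the documents support neither.

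- **That nine in ten respondents would have no follow-up score.** Results, Stage 4 says "The returning visitor rate is approximately 10" per cent. This is a web-analytics rate for all visitors from January 2019 to October 2020, before release of the interactive part. It does not measure follow-up among questionnaire respondents.
- **That working without pairs needs 2 to 3.3 times as many respondents.** The factor 1/(1 − r), for an assumed before-after correlation r of 0.5 to 0.7, holds only when the two samples are equal in size. With N first scores and 0.1N later scores treated as independent, the variance of the difference is s²/N + s²/(0.1N) = 11s²/N. The paired variance in the 0.1N with both scores is 2(1 − r)s²/(0.1N) = 20(1 − r)s²/N. The ratio is 11/10 = 1.1 at r = 0.5, 11/8 = 1.4 at r = 0.6 and 11/6 = 1.8 at r = 0.7. Precision is not the main issue here.

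**Conclusion.** The point holds as a mismatch between an anonymous data source and a change outcome. Followed on its natural reading, the Stage 4 BDKS outcome cannot separate learning from who responds. The possible artefact runs from zero to about 0.6 SD over the assumed range in the table. The response proportions and odds ratios are assumptions, and the documents neither confirm nor exclude any of them.

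A reader might infer that linkage is impossible in this study, or that its knowledge results in general are unsound. Neither follows. Accounts and pseudonyms exist and could be used, and the Stage 3 BDKS comparison rests on coded participants with defined time points. The effect is confined to a secondary assessment of the platform, for which the article states no hypothesis or sample size. This is a minor-to-moderate point, worth correcting because correction is cheap and cannot be made after the data are collected.

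**What to change.** Choose one of two routes and state it in Methods, Stage 4.

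1. **Keep the improvement outcome.** Make the Stage 4 BDKS pseudonymous, linked by a self-generated code or a pseudonymised platform login. Collect it at first use and again at a stated later time. Analyse within-person change in users with both scores. Compare first BDKS scores of users with and without a later score, and report the result as applying to those who answered twice.
2. **Keep full anonymity.** Report BDKS as a cross-sectional level and remove improvement from the outcome. Take knowledge change in platform-only patients from the coded Stage 3 control group, and say that this is change without a no-platform comparator. The informative part of the platform was live before Stage 3 recruitment began, so also record whether control participants had used it before their first assessment.

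Under either route, say plainly whether the anonymity statement covers the BDKS or only the satisfaction items. The Design section describes Stage 4 as ongoing, so any BDKS answers already gathered without a code can be used only as a cross-sectional level.

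Route 1 costs one code field, a sentence in the consent text and slightly less anonymity for those who answer. Route 2 costs a change of wording and the loss of a change claim for the wider group of platform users.

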### Patient and Public Involvement

Although patients with BD have not been included as members of the present research team, their input in the development of this study will be constant and accounted for during various stages of this project. Patient/participant involvement is registered as follows. Once enrolled in the study, participants’ feedback and reactions will be collected by the research team and used for improvement of the implementation of the study protocol. Respect for the rights, experiences, and personalities of the patients involved is one of the key priorities and motivations of the research team. During stage 1, the qualitative (empirical) exploration of the educational needs of patients with BD will be assessed. During the development of the MoB in-person intervention, the features, methods, and stages described by the participants (data from Stage 1) will be taken into account. Participant perspectives will also be addressed during preparation of the research questions on the effectiveness of the MoB in-person intervention. These questions are expected to be finalized according to the preliminary input resulting from the participants’ narratives on the clinical areas that need to be addressed by the MoB in-person intervention and the expected impact of the intervention on their lives (data from Stage 1). The issue of the participants’ burden of the MoB in-person intervention is included in the interview guide. Relevant data were used to define the duration of the MoB in-person intervention and the assessment periods of the intervention (data from Stage 1). Τhe participants are expected to introduce the proposed study to their peers, since a snowball sampling technique will be applied in Stage 3 aiming to recruit the participants of the intervention and control group. Finally, the participants who will be involved in Stage 4 will assess the applicability of the MoB digital platform via qualitative and quantitative data.

Due to the limited population of the Republic of Cyprus, attracting an adequate number of participants for the study is one of the challenges faced. However, the research team will disseminate the call to patients and providers’ associations as well as through other available means to ensure patient participation.

Members of the public, or the significant others/family members of the participants, will not be involved in the study. However, should the intervention be considered successful, significant effort and work will be exerted to alleviate the effects of the stigma of BD in society, both in Cyprus and internationally. A collaborative effort will be undertaken by the researchers to engage with members of the public to highlight the experience of BD, and the significance and effectiveness of the MoB intervention.

### Registration and Ethics

This protocol was approved by the Cyprus National Committee of Bioethics (ΕΕΒΚ/ΕΠ/2018/27) on September 30, 2018, and was registered at the Research Committee Review board of the Ministry of Health of the Republic of Cyprus (5.34.01.7.6^Ε^/0490/2018) on February 18, 2019. Moreover, the research protocol has been registered in ClinicalTrials.gov (ID: NCT04643210). All participants have/will sign the consent form for participation in the study, which includes the parameter of data publication. The questionnaires included in this study protocol have been previously published elsewhere and all relevant references to the questionnaires are cited in the manuscript.

## Results

### Stage 1

#### Literature Review

The literature review has been completed, and these data have been published [14]. Specifically, 15 studies were included in the review, showing that effective management of BD was mainly based on the combination of pharmacotherapy and structured educational interventions. Participation in structured educational interventions was associated with improvement in global functionality, adherence to pharmacotherapy, and early detection of relapse symptoms, all resulting in reduced frequency of hospitalization and experiences of mental illness social stigma. However, none of the reviewed studies assessed important areas of functioning (ie, cognition, delinquency, and impulse control). In relation to the mode of the educational intervention, both digital and in-person interventions were identified. Regarding the structure of the reviewed educational interventions, the majority were developed according to modified versions of the Colom and Vieta model [33], and their duration ranged with 7-8 in-person sessions and 6-21 group sessions. Moreover, personal interventions were linked to an increased frequency of drop-off and decreased duration of positive effects compared with those of group-based interventions. However, additional research on the effectiveness of in-person interventions compared to group-based interventions was suggested. Although this review described evidence on the effectiveness of web-based educational interventions, relevant data were not sufficient or of adequate quality to further support their usefulness. Nevertheless, it was revealed that web-based interventions were associated with advantages such as availability throughout the day and subsequently more opportunities for participation, accessibility to a larger network of people, and cost-effectiveness. Moreover, web-based interventions were more attractive to those encountering social stigma and younger participants. Additionally, the vast majority of the studies reported on the increased patient satisfaction from participation in educational interventions, and the most frequent reasons for quitting these interventions were increased job demands, relapse, and lack of time. Moreover, those with a duration of illness of more than 15 years did not benefit significantly from educational interventions. In conclusion, this review suggests the need for further intervention studies in educating BD clinical groups, combining in-person and web-based interventions, and further assessment of their effectiveness in areas such as substance use, delinquency, and impulse control.

#### Empirical Qualitative Exploration of Educational Needs

Regarding the qualitative exploration of the educational needs of ill-health self-management skills in people diagnosed with BD, a total of 13 participants were interviewed (8 women, 5 men). Specifically, since participation in interviews was designed to include both personal and focus group modes, we completed one focus group with 6 participants and 7 personal interviews (May to September 2020). The simultaneous data collection and analysis of emerged themes allowed us to determine thematic saturation up to this sample size. Thus, we did not proceed to an additional focus group as intended. Moreover, the fact that the participants came from different educational, social, and professional backgrounds supported the criterion of data saturation. By April 2021, all three meetings had been completed with all 13 participants. Relevant data defined the design of the MoB intervention and are expected to be published by the end of 2021.

Specifically, the participants only partially described the main symptomatology and the risks stemming for inadequate management of BD, and subsequently the impact of BD on their lives; notably, none of the participants reported any type of participation in a structured educational intervention on BD. Furthermore, the internet was identified as the primary source of education about their illness, with health care professionals (ie, psychiatrists and mental health nurses) listed as the second, yet ineffective, source of knowledge. Regarding BD-related educational needs, the participants mainly focused on the necessity to become familiar with the pathophysiology and symptomatology of BD, but most importantly the etiology behind the onset of this disorder and the factors that might have triggered BD. Moreover, they clearly described their need to enhance their knowledge about pharmacotherapy, side effects, and the rationale behind particular types of psychotropic agents, as well as effective management of the adverse effects of pharmacotherapy. Substance use was also included in the agenda of the participants regarding their educational needs. Additionally, the participants reported their need to be educated on how to manage human/patient rights violations against them, mainly in relation to consent to treatment, participation in clinical decision-making, and capacity to make legal decisions. The participants also described their need to enhance knowledge about the therapeutic procedures applied in other countries, as well as in relation to complementary therapeutic options. Female participants expressed their need to learn more about the link between BD and reproductive and sex-life health issues, with focus on fertility and the link between pharmacotherapy side effects and menstrual disturbances, childbirth, and hormones regulation. Employment-related issues were also raised, especially with respect to lack of knowledge regarding sick-leave issues and disclosure issues about their health status to their employers and coworkers. The participants also provided input regarding the frequency, duration, and mode of educational sessions. Most importantly, the participants underlined their need to be practically educated on how to implement all of the provided information into their daily lives, and mainly on how to identify and self-manage (if possible) early symptoms to prevent relapse.

Regarding the above topics, those referring to (a) sexual and reproductive health, (b) patient/human rights, (c) employment issues, and (d) alternative and complementary therapeutic options were incorporated into the MoB intervention, since these topics were not included or adequately covered in the Colom and Vieta [33] module. Moreover, the participants’ suggestions about the frequency (once a week), duration (90 minutes per session/12 sessions), and mode (both personal and group-oriented options to participate in the MoB intervention, combination of in-person and online modules via a digital platform) were also taken into consideration during development of the MoB intervention.

Beyond educational needs, the participants spontaneously provided descriptions about social needs, and specifically expressed their need to belong to a certain group or society, as well as their willingness to support others in need. Based on this input, a session on social skills training and information about how to engage in volunteering was incorporated in the design of the MoB intervention.

### Stage 2

